#### Feasibility

Feasibility is operationalized as the extent to which the implementation strategies can be successfully used and carried out within a school setting. After the end of the implementation period, semi-structured interviews with each school principal and others that have participated in the implementation strategies are performed to explore their views on the feasibility of the implementation strategies. The interview will, among others, assess the feasibility for the implementation team to meet between workshops, the feasibility of participating in the workshops and the feasibility of the frequency and duration of the educational meeting and workshops.

#### Fidelity

Fidelity is defined as the degree to which the implementation strategies are implemented as intended by the research team. Fidelity is measured by assessing 1) adherence to the protocol, 2) amount of intervention strategies delivered and 3) quality of delivery. For the educational meetings and each workshop, a time-schedule is developed. The schedule includes a fidelity column where any deviations are noted. The research-team is responsible for monitoring whether the implementation strategies are delivered according to the protocol. Procedures for monitoring adherence include making notes in the fidelity column when deviations occur for example regarding time or content. Moreover, a research-log is kept describing deviations and possible reasons for deviations.

#### Barriers and facilitators

Information on barriers and facilitators that may influence the implementation process is collected during semi-structured interviews held at 12- and 24- months follow-up with all school principals who participate in the study. An interview guide will be developed for the purpose of the study and will include questions based on CFIR (http://www.cfirwiki.net/guide/app/index.html). The framework provides a pragmatic structure for analyzing implementation factors in complex, multi-level interventions. Examples include, questions related to the school management’s perception of the advantage of implementing the guideline versus usual practice.

#### Data management

All participants receive a code and data is de-personalised. The code is kept separate from the data in a secure and locked place. Data collected during the educational meetings and workshops are first written on paper and then entered into the database by the research-team. Original paper documentation is saved and stored securely at Karolinska Institutet to allow for quality control of electronic data entry. All electronic data is stored in password protected folders on a secure data server at Karolinska Institutet to avoid unauthorized access. Measures to prevent loss of data are taken using systematic back-up routines throughout data collection and by data storage on servers with complete data back-up on a daily basis. Access to data is restricted to the research personnel working directly with data entry or analyses.

#### Statistical methods

The hypothesis is that the participants in ARM 1 when compared to the participants in ARM 2 will demonstrate improvements in exhaustion over time, as their schools will demonstrate higher adherence to the recommendations of the guideline compared to schools in the control group. Secondary hypotheses are that ARM 1 participants when compared to ARM 2 participants will demonstrate significant improvements in experience of job-demands, work organisation and job contents, interpersonal relations and leadership, presenteeism, work performance, recovery, work-life balance, work engagement, self-perceived stress, self-rated health, sickness absence and psychosocial safety climate.

Intention-to-treat analyses will be performed and where relevant, compared to per-protocol analyses. The aim of the statistical analyses is to examine the between group differences over time in adherence to the recommendations of the guideline (implementation effectiveness) and in exhaustion and the other individual level outcomes. The outcome variable adherence to the recommendations of the guideline will be operationalized into level of adherence based on the questionnaire developed by the research team. We will use mixed effects regression models to test the hypotheses of between groups difference in exhaustion. This analysis will allow for the modelling of data on school personnel, nested within the schools. Moreover, mixed models structure allows for inter-personnel and inter-schools heterogeneity through random effects such as individual intercepts and slopes over time. If potential confounders are unevenly distributed and if this is likely to affect the results when the two arms are compared, these factors will be adjusted for in the analyses. Possible interaction effects on the outcomes will be checked for. If they are statistically significant, stratified analyses will be considered. Finally, exploratory analysis will be performed to compare schools with high adherence to the recommendations of the guidelines compared to schools with low adherence. These analyses will for example examine differential effects on exhaustion and secondary outcomes. In addition, we will examine potential moderators such as school size, stability in school management etc. A detailed statistical analysis plan will be developed in collaboration with a statistician prior to starting the data analysis.

Regarding the qualitative data, interviews will be digitally recorded and transcribed verbatim. The recordings and texts will then be cross-checked for accuracy by the research team. We will employ thematic analysis with a deductive approach according to CFIR for the analysis of the interviews [53]. In the first step, the transcripts will be read through and listed to get an overall insight into the content. In the second step, the text is explored in line with the aim of identifying barriers and facilitators and coded accordingly. In the third step, codes will be collated into potential themes. In the last steps, themes will be reviewed, defined and named. Analysis will be conducted by researchers of the research team who have not been involved in the implementation strategies, e.g. educational day or workshops.

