## Methods

### Assignment of interventions

#### Allocation

Primary schools are randomized to either ARM 1 or ARM 2 after stratification in blocks by municipality and school size (number of students per school). This is done by a computer-generated randomization-list. Randomization is conducted prior to the baseline measurement due to logistical reasons, as the educational meeting and workshops needed to be scheduled so that they fit with the individual planning of each school. An independent statistician, blind to the identity of the schools and not involved within the project, conducts the randomization. The project leader informs the educational board of the municipalities and the school principals by e-mail about their allocation. After assignments to implementation strategies, neither the school management or school personnel are blinded.

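### Covariate adjustment in the primary comparison depends on observed imbalance and a judgement about its effect, and the randomisation strata are not tied to the model

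*Protocol article*

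**What the plan says.** All places are in the protocol article.

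- **Model (Statistical methods).** "We will use mixed effects regression models to test the hypotheses of between groups difference in exhaustion". Personnel are nested in schools, with "random effects such as individual intercepts and slopes over time". No fixed covariates are named.
- **Adjustment (same section).** "If potential confounders are unevenly distributed and if this is likely to affect the results when the two arms are compared", then "these factors will be adjusted for in the analyses". No variables, no measure of imbalance and no criterion for an effect on the results are given.
- **Interactions (same section).** Unnamed interactions are to be checked. "If they are statistically significant, stratified analyses will be considered".
- **Randomisation (Allocation; also Trial design).** "Primary schools are randomized to either ARM 1 or ARM 2 after stratification in blocks by municipality and school size". In the analysis, school size appears only in an exploratory role: "we will examine potential moderators such as school size, stability in school management etc". Municipality does not appear there at all.
- **Baseline (Outcome measures, intervention effectiveness).** Exhaustion is defined as change from baseline at 6, 12, 18 and 24 months.
- **Order of events (Allocation; Methodological considerations).** Schools were randomised before baseline was measured, and management and personnel knew the allocation. The authors list the early randomisation as a weakness.
- **Deferral (Statistical methods).** A detailed statistical analysis plan is promised before the data analysis starts.

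**The concern.** The issue is a rule that the article states, not a detail that it leaves out. The rule makes the content of the primary model depend on two judgements made on the data: whether some variable looks unevenly distributed, and whether that matters for the comparison. The second is the weaker safeguard, because one way to judge it is to fit the model with and without the variable and look at the treatment effect. Two analysts who both follow the text could report different primary results.

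The order of events makes observed imbalance a poor trigger here. Questionnaires were first completed after unblinded allocation, so a difference at baseline may partly reflect who enrolled and how they answered, not chance alone. Municipality and school size cannot be affected by allocation and were thought important enough to stratify on. Study setting shows how far they differ: seven schools with 200 to 800 pupils in one municipality, and 13 schools with 15 to 500 in the other. Yet the only covariate rule in the text does not reach them unless they happen to look imbalanced, which stratification is meant to prevent.

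At stake are the error rate of the primary test, some precision, and the credibility of a result from about 20 schools.

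**Working it through.** **Inputs from the article (Sample size, Trial design).** ICC 0.005; about 400 people, 200 per arm; at least 18 schools (20 in the trial); 80% power; significance level 0.05.

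**Assumed, because the article does not give them.** Two-sided test; equal school sizes; baseline/follow-up correlation r from 0.5 to 0.7; an effect of 0.30 SD, used only to check the sample size.

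**1. The plan's own figure.** The total of 400 cannot be reproduced from the article alone, because no SD or control rate accompanies the 30% improvement.
- People per school: 400/18 = 22.2. Design effect: 1 + (22.2 − 1) × 0.005 = 1.106.
- Reading 30% as 0.30 SD: 175 per arm × 1.106 = 194 per arm, 388 in total, within 3% of 400.

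This supports using 22.2 people per school and an ICC of 0.005 in step 3.

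**2. Error rate of the adjustment rule.** Data were simulated with no treatment effect: 18 schools, 22 people each, ICC 0.005, 8,000 runs. School means were compared by t-test. The only candidate covariate was the baseline score. The Monte Carlo standard error near 5% is √(0.05 × 0.95/8000) = 0.24 percentage points.

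| Policy | r = 0.5 | r = 0.7 |
|---|---|---|
| Never adjust | 5.1% | 4.8% |
| Always adjust | 4.8% | 5.1% |
| Adjust only if baseline differs at p < 0.05 | 4.4% | 3.6% |
| Take the better of adjusted and unadjusted | 7.6% | 8.3% |

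Either fixed policy holds 5% within simulation error. The mechanical rule is conservative. Free choice between two results inflates the error to about 8%. The article's wording does not say which of the last two rows describes the trial.

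**3. Cost of leaving out the strata.** The between-school share of the variance of an arm mean is 22.2 × 0.005/1.106 = 0.100. If municipality and school size explained all of it, the variance would fall to (1 − 0.005)/1.106 = 0.90 of its value. The loss is therefore at most about 10%. The bound depends on the ICC: at an assumed 0.02 it would be 22.2 × 0.02/(1 + 21.2 × 0.02) = 0.444/1.424 = 31%.

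**4. Baseline handling.** For a simple two-point comparison, the variance of a baseline-adjusted analysis relative to a change score is (1 − r²)/(2(1 − r)) = (1 + r)/2. This gives 0.75, 0.80 and 0.85 for r = 0.5, 0.6 and 0.7. The planned analysis is a mixed model over five measurement points, and the article does not say how baseline enters it. These ratios show what could be lost, not what the plan loses.

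**The case against.** The best defence is that this is a condensed article that promises a detailed analysis plan before analysis begins, and that covariate lists usually belong there. As to the list, that stands: not naming municipality, school size or baseline exhaustion as model terms would be no finding by itself, and nothing in the text excludes them. It does not rescue the adjustment rule, which the article fixes and which a faithful analysis plan would carry forward. Before analysis is also not the same as before outcome data exist. The second condition can be read as prognostic relevance and not as a look at the treatment effect. That reading is fair, but the text does not secure it.

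Several stronger readings are tempting and are not supported:

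- **That the rule invalidates the nominal error rate.** A reader might infer this, but the mechanical version is conservative. Inflation needs the analyst to pick the better result, which the article permits but does not state.
- **That some imbalance is nearly certain.** With ten candidate variables, 1 − 0.95^10 = 40% would show at least one difference at p < 0.05. The article names neither ten variables nor such a test, the formula assumes independence, and 40% is not an error rate for the treatment effect.
- **That omitting the strata makes the standard errors too small.** The model already allows schools to differ through random effects, and leaving out balanced strata tends to make standard errors too large.
- **That baseline exhaustion is ignored.** It enters through change from baseline in a repeated-measures model. A comparison with unadjusted follow-up scores would describe an analysis that nobody proposes.
- **That a significant interaction would replace the overall result.** The article says only that stratified analyses would be considered.

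**Conclusion.** The point holds as a cheap improvement that should be made, not as a fatal flaw. The article states a data-dependent adjustment rule without variables or criteria, in a trial where school management and personnel are unblinded, and does not link its stratification factors to the primary model.

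Under 18 equal schools, ICC 0.005, r of 0.5 to 0.7 and a single candidate covariate, the type I error lies between about 4% and about 8%, depending on how the rule is used. The strata are worth at most about 10% of variance at the stated ICC. The main reason to include them is that the analysis should follow the design. A gain from explicit baseline adjustment is plausible, but its size cannot be established from the article.

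**What to change.** Replace the conditional sentence in Statistical methods, and carry the change into the analysis plan, along these lines:

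- The primary mixed model includes arm, time, arm by time, municipality and school size (as used in the randomisation), and baseline exhaustion, whatever imbalance is observed. Baseline enters either as a covariate or as a first outcome with arm means constrained to be equal. State which; the second form also keeps people without a T0 score.
- Because baseline was measured after unblinded allocation, the model with the strata only, without conditioning on baseline, is reported as a sensitivity analysis. This matters most for the constrained form, which assumes equal arms at T0.
- Any adjustment prompted by observed imbalance is a named sensitivity analysis and does not alter the primary result.
- The overall intention-to-treat effect remains the result whatever the interaction tests show. Interactions are prespecified and reported as estimates with confidence intervals.

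The cost is wording and no new data. Municipality takes one school-level degree of freedom and school size one or two, depending on the bands used, so about 2 to 3. With 20 schools and two arms, that leaves 15 or 16 of 18.

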
A randomized controlled trial with two arms will be conducted comparing an implementation intervention with a single strategy versus one with multifaceted strategies (educational strategy, implementation teams and workshops). Information will be collected on both implementation effectiveness, and intervention (guideline) effectiveness (i.e. reduction of risk factors for mental ill-health). This will provide valuable knowledge on whether adherence to the recommendations in the guideline will result in reductions in employees’ perceived social and organizational risk factors, mental ill-health and sick-leave. The programme theory is depicted in Fig. 1. The trial will be conducted within schools with the aim to prevent mental ill-health and sick leave among teachers. Globally, teachers have a high prevalence of CMDs and related sick-leave [37–39].

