### Trial design

The study is a 12-month cluster-randomized waiting list-controlled trial with before and after measurements involving 20 primary schools in two municipalities in Sweden. Randomization (1:1 allocation to intervention and waiting list control) is conducted at the school level. Primary schools are randomized by a computer-generated randomization-list to either the ARM 1 or ARM 2 after stratification in blocks by municipality and school size (number of students per school). Schools in ARM 1 will receive all three implementation strategies during the first year of the study period while schools in ARM 2 will receive only the educational strategy in year 1 and continue with the other strategies during year 2 (Fig. 2). The implementation strategies target the managerial level of first line managers i.e. school-principals. All employees of the participating schools will be invited to complete outcome-questionnaires at baseline and 6-, 12-, 18- and 24-months follow-up during working hours.

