### Sample size

The power-calculation for the proposed study is calculated on the effectiveness on employee-level (intervention effectiveness). In order to achieve 80% statistical power and a significance level of *p* < 0.05 to be able to detect an improvement in the primary outcome exhaustion with 30% among employees in the intervention group compared with employees in the control group, an intra-cluster correlation has been weighted (ICC = 0.005) and about 400 people in total are required (200 people in the intervention group and 200 people in the control group). This required the participation of at least 18 schools.

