The school management ((assistant) - school-principal) complete a questionnaire containing statements related to the guideline’s recommendations. Nine items (5-point Likert Scale: “fully disagree”- “fully agree”; and do not know) are used to assess adherence to recommendation 1: *Workplaces should have well-established policies related to the social and organizational risk management* (e.g. The introduction of new employees includes a briefing of the school’s working environment document). Adherence to recommendation 2: *Employers should have knowledge on the relationship between social and organizational risks and mental ill-health* is assessed with five items (5-point Likert Scale: “fully disagree”- “fully agree”; and do not know) (e.g. We have written documents stating what the school-management needs to know regarding how the work environment affects mental ill-health). Ten items are used to assess adherence to recommendation 3: *Workplaces should regularly assess their social and organizational work environment and intervene on identified social and organizational risk factors* (5-point Likert Scale: “fully disagree”- “fully agree”; and do not know) (e.g. In the last assessment of social and organisational risk factors at the workplace, the school management and employees together developed an action plan for improvement of identified social and organisational risks at the workplace). Moreover, one item (multiple-choice) assesses when the last assessment of the social and organisational work environment had taken place.

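### The one described analysis relating adherence to outcomes splits 18-20 schools into high and low groups, although adherence is measured on a graded scale

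*Protocol article*

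**What the plan says.** Statistical methods in the protocol article states that "exploratory analysis will be performed to compare schools with high adherence to the recommendations of the guidelines compared to schools with low adherence", and adds: "These analyses will for example examine differential effects on exhaustion and secondary outcomes". No cut-point, group size or power is given for this analysis. The same section says that adherence "will be operationalized into level of adherence based on the questionnaire developed by the research team", and that a detailed SAP will be written before data analysis starts.

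The instrument is set out under Outcome measures (implementation effectiveness). For management, "Nine items (5-point Likert Scale: “fully disagree”- “fully agree”; and do not know) are used to assess adherence to recommendation 1". Five items on the same scale cover recommendation 2, and "Ten items are used to assess adherence to recommendation 3", again on five points. Staff answer 3 + 1 + 9 similar items.

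Trial design describes a study "involving 20 primary schools in two municipalities in Sweden". Sample size says: "This required the participation of at least 18 schools". Background and rationale expects the trial to show "whether adherence to the recommendations in the guideline will result in reductions in employees’ perceived social and organizational risk factors, mental ill-health and sick-leave".

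**The concern.** The form of this contrast is stated, not left open: two groups of schools. The unit that carries adherence is the school, and there are at most 20. Splitting them treats a school just above the cut as equal to the best school and as different from its neighbour just below. The result can also depend on where the cut falls.

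The main hypothesis runs through adherence: exhaustion should improve in ARM 1 because its schools adhere better. The arm comparison cannot show that link, so the exploratory comparison is what remains to inform it. If the multifaceted strategy works, high-adherence schools will mostly be ARM 1 schools. A two-group split then leaves little contrast within arms with which to tell adherence from allocation.

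**Working it through.** **Inputs from the article.** 20 schools planned and at least 18 required; about 400 staff; ICC 0.005; 80% power; p < 0.05; a 30% improvement in exhaustion. Management items: 9 + 5 + 10 = 24. Staff items: 3 + 1 + 9 = 13.

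**Assumed, because the article does not give them.** A two-sided test, a median split, roughly normal adherence within arm, equal school sizes, and 30% read as 0.30 SD.

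**The plan's own figure.** There is no stated power for the adherence analysis. For the arm comparison, a 0.30 SD difference needs about 175 per arm without clustering. With 400/18 = 22.2 staff per school the design effect is 1 + 21.2 × 0.005 = 1.106, and 175 × 1.106 ≈ 194 per arm. That is close to the stated 200, so 0.30 SD is a workable reading, although no SD or base rate confirms it.

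**Step 1: cost of a median split for a given correlation.** School-level data were simulated with correlation r between adherence and outcome (at least 40,000 runs). The t-test for linear association was compared with the t-test between halves. Power is in %; losses are in points, taken before rounding.

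| r | 20 schools: graded / split / loss | 18 schools: graded / split / loss |
|---|---|---|
| 0.3 | 25 / 17 / 8 | 23 / 15 / 8 |
| 0.4 | 43 / 28 / 15 | 39 / 25 / 14 |
| 0.5 | 64 / 43 / 22 | 59 / 38 / 21 |
| 0.6 | 84 / 60 / 23 | 79 / 55 / 24 |
| 0.7 | 96 / 79 / 17 | 93 / 73 / 20 |

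Across repeated runs the loss was about 7 to 25 points. Outside this range it shrinks: 1 to 3 points at r = 0.1 to 0.2, 7 to 10 at r = 0.8, and about 1 at r = 0.9. Other cuts also lose power at r = 0.3 to 0.7: 6 to 17 points for extreme thirds with the middle dropped, 10 to 36 for a top-quarter group.

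**Step 2: what the article's ICC implies without an arm effect.** With m = 20 staff per school, the between-school share of the variance of a school mean is m × ICC / (1 + (m − 1) × ICC) = 0.10 / 1.095 = 0.091. Even if adherence explained all of it, r could not exceed √0.091 = 0.30. Power is then about 26% graded against 17% split, a loss of about 8 points.

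**Step 3: the article's ICC with the arm effect acting wholly through adherence.** Take 20 schools of 20 staff and hold the within-arm ICC at 0.005. The within-arm variance of a school mean is 0.005 + 0.995/20 = 0.0548.

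- *Adherence explains all the within-arm school variance.* The slope is √0.005 = 0.0707 SD of outcome per within-arm SD of adherence, so the arms must differ by 0.30/0.0707 = 4.2 such SDs. Unadjusted power is about 87% graded against 78% split (loss about 9). Adjusted for arm, the graded score has about 24-25%.
- *Adherence explains half of it.* The slope is √0.0025 = 0.05 and the arms differ by 0.30/0.05 = 6 SDs. Unadjusted power is about 82% against 77% (loss about 5). Adjusted for arm, the graded score has about 14%.

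In both cases the median split coincides exactly with the arms in over 90% of runs. A high/low term and an arm term cannot then both be estimated. The split's 77-78% is in effect the power of the arm comparison: 0.30/√(2 × 0.0548/10) = 0.30/0.105 ≈ 2.9 standard errors.

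**The case against.** The strongest reply is that this is one sentence about an exploratory, non-randomised analysis. The article gives no cut-point and promises an SAP, and the wording could be loose shorthand for an association. The article sets no power target here, so a power loss breaks no promise. The trial's conclusions rest on the randomised comparisons of exhaustion and adherence. Much of this stands, and it limits the weight of the point. It does not remove it: the article names a two-group contrast of schools, and an SAP that follows the sentence inherits it.

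A second reply is that graded coding does not rescue the analysis. That also stands for the arm-adjusted slope. At the article's ICC its power is about 14-25%, limited by the number of schools and the small between-school variance rather than by coding.

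Three stronger readings are tempting and are not supported:

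- A reader might take 7 to 25 points as the general price of the split. It depends on a median cut and on r of about 0.3 to 0.7. At the article's ICC the loss is nearer 5 to 9 points.
- A reader might infer that continuous adherence would have good power after adjustment for arm. That needs far more between-school variance within arms than an ICC of 0.005 allows.
- A reader might take the phrase about level of adherence to mean categories. A mean score is also a level, and the article does not say otherwise.

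**Conclusion.** The point holds in modest form. The only described quantitative adherence-outcome analysis discards information from a graded score on 18-20 schools, and the graded score had higher power in every scenario computed. The loss is about 7 to 25 points for a median split with r of about 0.3 to 0.7, and less outside that range. It is about 5 to 9 points unadjusted at ICC 0.005 with a fully mediated 0.30 SD effect and 20 schools. In that last setting the larger problem is interpretation: the split nearly duplicates the arms and says almost nothing about adherence beyond allocation. All these sizes rest on the assumptions listed in the working. The primary analysis is not touched.

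**What to change.** In Statistical methods, and in the SAP, replace the high-versus-low comparison with school mean adherence as a continuous school-level covariate in the planned mixed model with a random school effect. Report the slope with its 95% CI, once without arm and once with arm. Keep high and low groups for descriptive display only. Keep the exploratory label, and state that the arm-adjusted slope will be imprecise with about 20 schools, so that a wide interval is not read as absence of a link.

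The cost is a sentence or two and no new data. The small downside is an assumption of rough linearity, which a plot of the school means can check.
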